# Radiotherapy versus low-dose tamoxifen following breast-conserving surgery for low-risk and estrogen receptor-positive breast ductal carcinoma in situ: an international open-label randomized non-inferiority trial (TBCC-ARO DCIS Trial)

**DOI:** 10.1186/s12885-023-11291-6

**Published:** 2023-09-14

**Keywords:** Ductal carcinoma in situ, Breast, Tamoxifen, Radiotherapy, Low-risk

## Abstract

**Background:**

Radiotherapy (RT) following breast-conserving surgery (BCS) is mainly used to decrease the rate of ipsilateral breast tumor recurrence (IBTR) in women with breast ductal carcinoma in situ (DCIS). Recent studies have demonstrated that low-dose tamoxifen significantly reduces IBTR in breast DCIS. Here, we aim to determine whether the administration of low-dose tamoxifen is non-inferior to RT in preventing IBTR in patients with low-risk characteristics of breast DCIS.

**Methods/design:**

This is a prospective, international, open-label, randomized, non-inferiority trial. Patients with low-risk clinicopathologic features (> 40 years old, low risk of breast cancer susceptibility gene (*BRCA) 1* and *BRCA2* mutations, mammographically detected unicentric and non-mass lesions, low- or intermediate-grade without comedo or necrosis, measuring < 2.5 cm with margins ≥ 3 mm, and estrogen receptor-positive status) of DCIS who underwent BCS will be randomized at a 1:1 ratio to either receive tamoxifen (5 mg/day) for 5 years or undergo RT with conventional fractions (50 Gy in 25 fractions) or hypofractionations (40.05 Gy in 15 fractions). Randomization will be stratified by the Taiwan Breast Cancer Consortium. As approximately 5% of patients cannot tolerate the side effects of low-dose tamoxifen and will receive RT, we estimate that 405 patients will be randomized to a low-dose tamoxifen arm and 405 patients to the RT arm, according to a non-inferiority margin within 5% of IBTR difference and 90% β-power noticing non-inferiority. The primary endpoints are breast tumor recurrence, including ipsilateral, regional, contralateral, and distant recurrence of breast DCIS or invasive cancer. The secondary endpoints are overall survival and adverse effects of RT and tamoxifen. Translational studies will also be conducted for this trial.

**Discussion:**

This is the first non-inferiority trial on breast DCIS. This study will provide an important recommendation for clinical physicians on whether to use low-dose adjuvant tamoxifen for patients with low-risk breast DCIS who do not want to receive adjuvant RT.

**Trial registration:**

ClinicalTrials.gov, ID: NCT04046159, Registered on April 30, 2019.

**Supplementary Information:**

The online version contains supplementary material available at 10.1186/s12885-023-11291-6.

## Background

### Background and rationales

#### Low-risk characteristics of breast ductal carcinoma in situ (DCIS)

Radiotherapy (RT) following breast-conserving surgery (BCS) is commonly used to decrease local recurrence of breast ductal carcinoma in situ (DCIS) [1]. However, previous retrospective studies suggest that certain patients with breast DCIS who had low-risk characteristics and underwent BCS alone do not develop a recurrent invasive breast cancer or DCIS over time [2]. To identify a substantial proportion of breast DCIS patients with low-risk characteristics who can be spared adjuvant RT, two prospective trials, including the Eastern Cooperative Oncology Group (ECOG) E5194 and one trial designed by Dana Farber/Harvard Cancer Institute, and one randomized trial (Radiation Therapy Oncology Group [RTOG] 9804), enrolled breast DCIS patients with low-risk characteristics, including lower histological grade, smaller size, and larger margin width, and reported the ipsilateral breast tumor recurrence (IBTR) rate in this subgroup of patients [3–6].

In the Dana Farber/Harvard Cancer Institute trial, Wong et al. showed that the 5-year IBTR rate was 12% in breast DCIS patients who met the criteria of low- to intermediate-grade disease, had a margin width of 10 mm, and had undergone BCS alone [3]. In the E5194 trial, 7-year and the 12-year IBTR rates of 10.5% and 14.4%, respectively, were observed in patients with low-risk cohort-1 breast DCIS (cohort 1 criteria: mammographically detected low- or intermediate-grade DCIS, measuring < 2.5 cm with surgical margins ≥ 3 mm) who underwent BCS alone [4, 5]. Notably, the risk for developing DCIS and invasive cancer in low-risk cohort-1 breast DCIS of the ECOG trial increased gradually over time without plateau [4, 5]. In a randomized trial of RTOG 9804 comparing the occurrence of IBTR among patients who underwent RT and were observed for breast DCIS with similar tumor characteristics in cohort 1 of the ECOG E5194 trial, McCormick et al. showed that IBTR rates were higher in those without RT than in those with RT (7-year IBTR rate, 6.7% vs. 0.9%, *P* < 0.001) [6]. In our cohort of 150 breast DCIS patients who underwent BCS alone and whose clinicopathological features met the criteria of cohort 1 of the ECOG E5194 trial, we found a 7-year IBTR rate of 5.6% [7]. Based on the data from the ECOG E5194 and RTOG 9804 trials and our cohort study, the 7-year IBTR rate ranged from 5.6%–10.5% in breast DCIS patients who underwent BCS alone and had low-risk characteristics [4–7], indicating that RT following BCS is still desirable for patients who had pathological features similar to ECOG E5194 cohort 1.

The randomized trial UK/ANZ (UK, Australia, and New Zealand) DCIS trial, which enrolled breast DCIS patients irrespective of low-risk or high-risk characteristics, showed that among patients who underwent BCS alone, administration of tamoxifen (20 mg/day for 5 years) significantly reduced ipsilateral (Hazard ratio [HR], 0.77; 95% confidence interval [CI], 0.59–0.98; *P* = 0.04) and contralateral breast events (HR, 0.27; 95% CI, 0.12–0.59; *P* = 0.001). However, the benefit of tamoxifen in reducing ipsilateral breast events (HR, 0.93; 95% CI, 0.50–1.75; *P* = 0.8) was not observed in the BCS plus RT group [8]. These findings suggest that the addition of tamoxifen after RT may not reduce IBTR in breast DCIS patients who had low-risk characteristics, like in cohort 1 of the ECOG E5194 trial. However, the association between IBTR and estrogen receptor (ER) status in tumors of patients with DCIS who entered the aforementioned trials was not assessed [4–6, 8].

Among 732 patients (41%) with breast DCIS who received tamoxifen from the original National Surgical Adjuvant Breast and Bowel Project B-24 population, in which ER-positive tumors were 76%, Allred et al. showed that tamoxifen administration significantly diminished ipsilateral and contralateral recurrent breast events in those with ER-positive tumors, but did not impede recurrent events in those with ER-negative tumors [9]. In addition, we observed that among breast DCIS patients who underwent BCS alone, age < 40 years and negative ER status in tumors were two prognostic factors for increasing IBTR [7]. Our study also revealed that, even among breast DCIS patients who had pathological features similar to those in cohort 1 of the ECOG E519 trial, ER-negative status was associated with a trend of higher 7-year IBTR (8% vs. 5%, *P* = 0.69) [7].

### Objectives

The aim of this study is to explore whether the clinical efficacy of administration of tamoxifen (5 mg/day) for 5 years following BCS is not inferior in reducing recurrence of breast events when compared with RT following BCS in breast DCIS patients with low-risk clinicopathologic features and positive ER status in tumors.

### Trial design

The study outline of the Taiwan Breast Cancer Consortium (TBCC)- Japan Academic Research Organization (ARO) is a prospective, international, open-label, randomized, non-inferiority trial. A flowchart of the TBCC-ARO DCIS trial is shown in Fig. 1. Patients aged > 40 years with low-risk characteristics of breast DCIS and who have undergone BCS may be enrolled in this study and will be randomly assigned to either the RT or low-dose tamoxifen groups for 5 years.

**Fig. 1 Fig1:**
[figure not shown]
Schematic diagram of the design of an international open-label randomized non-inferiority trial of whole breast radiotherapy versus low-dose tamoxifen for low-risk and estrogen receptor-positive breast ductal carcinoma in situ after breast conserving surgery. Abbreviations: DCIS, ductal carcinoma in situ; BCS, breast conserving surgery; SNP, single nucleotide polymorphism

### Methods: participants, interventions, and outcomes

#### Study setting

This international trial consists of 11 participating medical centers: 9 sites from the TBCC and 2 sites from the ARO.

### Eligibility criteria

#### Inclusion criteria

New histologically diagnosed breast DCISAge ≥40 yearsLow risks of *BRCA1* and *BRCA2*: Manchester Score < 10 (Supplementary Table 1) [14, 15].DCIS must be detected by a mammogram and must be unicentric, with non-mass lesionsStatus post-BCSPathological characteristics:6.1Lesions ≤2.5 cm in the greatest dimension on pathology specimens (use the largest measured size from the pathology report to obtain the required measurement of ≤2.5 cm)6.2Must be classified as low or intermediate nuclear grade DCIS but without comedo or necrosis, according to the Pathologic Guidelines [16, 17].6.3Margins, as assessed by the ink method, should be ≥ 3 mm.6.4Must be ER-positive DCIS, and the ER percentage must be ≥ 10%Clinically node-negative

#### Exclusion criteria

Known *BRCA1* or *BRCA2* mutationsWomen whose DCIS is palpable at the time of diagnosis, multicentric (mammography), mass (mammography), or bloody nipple dischargePathological characteristics:3.1Lesions measuring >2.5 cm in the greatest dimension on pathology specimens3.2High-grade lesions or low- to intermediate-grade with comedo or necrosis classified according to the Pathologic Guidelines [16, 17].3.3Margins, as assessed by the ink method, were < 3 mm.3.4ER-negative DCIS or ER-positive percentage < 10% in tumor cellsPost-mastectomy patients.Prior diagnosis of neoplasm within 5 years, except for cervical intraepithelial neoplasia 1 or localized non-melanomatous skin cancerEvidence of clinically significant cardiac disease, as defined by cardiac disease (New York Cardiac Disease Grade II), history of myocardial infarction, cerebral stroke, unstable arrhythmia, and unstable angina pectoris within 12 months before study entry

### Interventions

#### Intervention description

In the current study, patients who are randomized to the RT arm will undergo RT with 50 Gy divided in 25 fractions (2 Gy each) or with 40.05 Gy divided in 15 fractions (2.67 Gy each); RT dose and fractions will be dependent on the institution’s experience. RT for treating the whole breast will be delivered daily from Monday to Friday; however, regional lymphatic irradiation and boost of the tumor bed will not be allowed.

All patients randomized to the tamoxifen treatment arm will receive tamoxifen (5 mg/day) for 5 years. Tamoxifen toxicities, including hot flashes, transient nausea, and vaginal discharge, are minimal, whereas skin rash, vaginal bleeding, edema, and embolisms seldom occur. As the drug compliance of patients who are randomized to low-dose tamoxifen is crucial, the adherence to taking 5 mg tamoxifen was defined as the use of at least 90% of these pills each year for at least 5 years.

### Criteria for discontinuing or modifying allocated interventions

If the inclusion and/or exclusion criteria are contravened after recruitment, these patients will be removed from the trial. Dropouts from this trial will receive adjuvant RT with or without 20 mg tamoxifen based on clinicopathological features. For these patients, their clinical data and treatment characteristics will be retained, unless they unambiguously refuse.

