### Strategies to improve adherence to interventions

Participants will follow the recommendations of the study protocol, including the doses of RT and tamoxifen. Because the study is divided into two arms, adjuvant RT and adjuvant low-dose tamoxifen, deviations in the RT or tamoxifen doses will not be allowed. If participants refuse the assigned treatment, they will remain in the trial’s intention-to-treat analysis, unless they unambiguously refuse.

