### Outcomes

Our primary objective is to observe breast tumor recurrence, including ipsilateral, regional, contralateral, and distant recurrences of breast cancer (DCIS or invasive cancer events).

Our secondary objective is to assess overall survival in all patients, adverse effects of RT and tamoxifen, and translational studies—including single nucleotide polymorphisms (SNPs), extracellular matrix (ECM)- and immune-related molecules, and mutational analyses of selected genes.

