### Assignment of interventions: determining who will be blinded

The current protocol of the TBCC-DCIS trial is an international, open-label, randomized, non-inferiority trial. Therefore, no blinding is planned.

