### Statistics

#### Statistical methods for primary and secondary outcomes

In this study, patients who do not follow the protocol of their assigned treatment arm will not be analyzed. We will use the chi-square test, Student’s *t*-test, and Fisher’s exact test to compare the clinical characteristics between patients undergoing RT and those receiving low-dose tamoxifen. In this study, we will use the Kaplan–Meier method to estimate the time to IBTR (only breast area), ipsilateral regional recurrence of lymph nodes (including axillary, supraclavicular, or internal mammary lymph nodes), contralateral breast local recurrence, and distant metastases from the date of surgical excision. In addition, we will use this method to calculate overall survival, which will be measured from the date of surgical excision to the date of death from any cause or to the date of the last follow-up. Comparisons between the patients will be performed using the log-rank test. All statistical analyses will be carried out at a 5% significance level.

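### Randomized patients found ineligible at any later time are removed from the trial, and nothing in the protocol keeps them in follow-up or in the primary analysis

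*Protocol article*

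**What the plan says.** The rule stands in the protocol article under *Criteria for discontinuing or modifying allocated interventions*: "If the inclusion and/or exclusion criteria are contravened after recruitment, these patients will be removed from the trial". Two sentences follow it. One covers treatment: "Dropouts from this trial will receive adjuvant RT with or without 20 mg tamoxifen based on clinicopathological features". The other covers data: "For these patients, their clinical data and treatment characteristics will be retained, unless they unambiguously refuse".

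Two other sections bear on who is analysed:

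- *Strategies to improve adherence to interventions* keeps patients who refuse their assigned treatment in the "intention-to-treat analysis, unless they unambiguously refuse".
- *Statistical methods for primary and secondary outcomes* says that "patients who do not follow the protocol of their assigned treatment arm will not be analyzed".

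On blinding the article says: "Therefore, no blinding is planned". *Implementation* places randomization directly after registration, and *Plans for assessment and collection of outcomes* sets 10 years of follow-up. *Outcomes* defines the primary endpoint as "breast tumor recurrence, including ipsilateral, regional, contralateral, and distant recurrences of breast cancer".

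**The concern.** Because randomization follows registration directly, most findings made after recruitment are also made after randomization. The rule sets no date after which it stops applying. It does not require that the disqualifying fact was already true at randomization, or that whoever decides is unaware of arm and outcome. Over 10 years, with the arm known to everyone, removal could depend on what happened to the patient.

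A relapse can prompt a second look at the index pathology or at genetic risk. Ineligibility that was there from the start may therefore come to light more often in patients who relapse than in those who do not. This is an inference and is not stated in the article. If it happens, the patients removed are disproportionately those with events, and the comparison is no longer between the groups as randomized.

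In a non-inferiority trial with few events, losing event patients shrinks the absolute difference that the margin is meant to limit. The issue is also distinct from the exclusion of non-adherers, since a patient later found ineligible may have followed her assigned treatment completely. Correcting the non-adherence sentence alone would leave this rule in force.

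**Working it through.** **1. What the text does with a removed patient**

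| Section | Whom it covers | What it settles |
|---|---|---|
| Criteria for discontinuing or modifying | Eligibility contravened after recruitment | Removed; data retained; analysis not mentioned |
| Strategies to improve adherence | Refused assigned treatment | Stay in intention-to-treat |
| Statistical methods | Did not follow the assigned arm's protocol | Not analysed |

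The intention-to-treat sentence does not reach patients found ineligible. No other sentence brings them back into follow-up or analysis.

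**2. Reproducing the design**

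Inputs from *Sample size* and Table 2: 6% in both arms at 7 years, margin 5 points, α 5%, power 90%.

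n = 2p(1−p)(z_α + z_β)²/Δ² = 2 × 0.06 × 0.94 × (1.645 + 1.282)²/0.05² ≈ 386.4, so 387 per arm. The stated figure is 385, which agrees closely. It reproduces only with a one-sided 5% test; one-sided 2.5% gives 475. Adding 5% gives 385 × 1.05 ≈ 404, close to the stated 405.

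Expected ipsilateral events per arm: 0.06 × 385 = 23.1, or 0.06 × 405 = 24.3.

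**3. How much one patient weighs**

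Upper one-sided 95% limit: U = p_T − p_R + 1.645 × √[p_T(1−p_T)/n_T + p_R(1−p_R)/n_R], with radiotherapy at 23/385 = 5.97%.

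- Tamoxifen 31/385 = 8.05%: U = 2.08 + 1.645 × 1.839 = 5.10 points. Fails.
- One tamoxifen event patient removed, 30/384 = 7.81%: U = 1.84 + 1.645 × 1.826 = 4.84 points. Passes.
- For balance, one radiotherapy event patient removed instead (22/384 against 31/385): U = 5.32 points, further from a pass.

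**4. Effect on false non-inferiority**

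True rates are set at the margin: 11% on tamoxifen, 6% on radiotherapy, 405 per arm. A fraction f of event patients is removed. The observed rate becomes p(1−f)/(1−pf) and the arm size 405(1−pf). The chance of a false claim is Φ[(0.05 − D)/SE − 1.645], where D is the difference after removal.

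Worked case, f = 10%:

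- Tamoxifen: 0.099/0.989 = 10.01%, n = 400.5. Radiotherapy: 0.054/0.994 = 5.43%, n = 402.6.
- Both arms: D = 4.58 points, SE = 1.878, Φ(0.225 − 1.645) = 7.8%.
- Tamoxifen arm only: D = 10.01 − 6.00 = 4.01 points, SE = 1.908, Φ(0.519 − 1.645) = 13.0%.

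| f | Event patients removed (tamoxifen / radiotherapy) | Equal removal in both arms | Tamoxifen arm only |
|---|---|---|---|
| 0 | 0 / 0 | 5.0% | 5.0% |
| 5% | 2.2 / 1.2 | 6.2% | 8.2% |
| 10% | 4.5 / 2.4 | 7.8% | 13.0% |
| 20% | 8.9 / 4.9 | 12.2% | 28.5% |

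The radiotherapy counts apply to the equal-removal column only. Equal removal still inflates the error because it shrinks the absolute difference while the margin stays at 5 points. Using 385 per arm changes little: 6.2%, 7.7% and 11.9% for both arms; 8.1%, 12.7% and 27.6% for tamoxifen only.

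**The case against.** A reader might go further and infer that a recurrence itself triggers removal, so that primary events are deleted. Some criteria carry no date. Read literally, a nodal recurrence breaches "Clinically node-negative", a mastectomy for relapse makes the patient post-mastectomy, and later testing can make a *BRCA* mutation known. The article does not support that reading:

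- Regional and other recurrences are part of the primary endpoint, and *Statistical methods* plans Kaplan–Meier estimates for each type. If they triggered removal, those outcomes could not be observed.
- The criteria describe the index lesion, its surgery and status at entry. Nothing ties removal to relapse.
- The reference to adjuvant radiotherapy suggests that the authors had early discovery in mind, such as a corrected pathology report.
- Deletion is too strong a word, since the data are retained. The article is silent on whether they are analysed.

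It is also fair to object that one-arm removal is only one scenario. Late findings can arise in either arm, and losing radiotherapy events works against a non-inferiority claim. That is why both cases are tabulated and neither is offered as a forecast.

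Finally, an article leaves much to the full protocol or analysis plan, and the lack of a blinded eligibility review would not by itself be a finding. What remains is that the article states an unconditional rule, removal from the trial. An analysis plan cannot restore follow-up that a site has already stopped. If early discovery was intended, the text should say so.

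**Conclusion.** The point holds as a defect in a stated rule. The protocol permits open-ended removal after randomization for ineligibility, decided in an open-label setting, and does not say that the retained data enter the primary analysis. It fits poorly with the intention-to-treat wording for refusers and with the exclusion of non-adherers.

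The size is conditional. A single excluded event can reverse a borderline result. At the margin, removing 5% to 20% of event patients raises false non-inferiority from 5% to between 6.2% and 12.2% if both arms are affected equally, and to between 8.2% and 28.5% if only tamoxifen is affected. These figures assume the removal fractions, a one-sided 5% Wald test on 7-year ipsilateral recurrence and no censoring. If late-found ineligibility is unrelated to outcome, the loss is mainly precision and there is no systematic bias.

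**What to change.** Replace the removal sentence with wording to this effect:

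- Eligibility is judged on the facts as they stood at randomization.
- Every randomized patient stays in follow-up and in the primary analysis, in the assigned arm, unless she withdraws consent.
- Ineligibility found later is recorded as a protocol deviation.
- Excluding ineligible patients is confined to a sensitivity analysis that uses only pre-randomization facts, judged by people who know neither arm nor outcome.

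Then reconcile the three sections on discontinuation, adherence and statistical methods so that they define one primary analysis set. How such patients are treated is for the sponsor to settle; no change is proposed here.

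The cost is about one paragraph. Data of removed patients are already retained, the sample size does not change, and only 36 patients had been enrolled by December 2022. The downside is that a few ineligible patients stay in the main analysis.

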### Strategies to improve adherence to interventions

Participants will follow the recommendations of the study protocol, including the doses of RT and tamoxifen. Because the study is divided into two arms, adjuvant RT and adjuvant low-dose tamoxifen, deviations in the RT or tamoxifen doses will not be allowed. If participants refuse the assigned treatment, they will remain in the trial’s intention-to-treat analysis, unless they unambiguously refuse.

### Relevant concomitant care permitted or prohibited during the trial

In this study, we will allow participants who take medication necessary for the performance of either examination or procedure and take previously prescribed medications before randomization.

### Provisions for post-trial care

For participants in Taiwan, treatments, including administration of tamoxifen and RT, and post-treatment follow-ups are covered by public health insurance.

